## Methods

### Study objectives

The objective of this implementation evaluation is to assess whether the MOUD 2.0 algorithm improves treatment adherence and retention in the treatment program at the clinic-wide level, compared to these outcomes before implementation. The primary outcome measures are quantified adherence to MOUD and time length of retention in the treatment program.

Adherence will be operationalized as having a minimum of 3 buprenorphine appropriate drug screens (resulting positive for buprenorphine and norbuprenorphine) over a 6-month period regardless of substance use. Retention in treatment will be measured as the proportion of participants with at least 180 days of continuous pharmacotherapy with a medication prescribed for OUD, with no gaps greater than seven days (22). These outcome measures will show whether retention rates increase along with adherence, or whether the implementation favors one outcome measure over the other. The two measures are not mutually exclusive. In the context of an implementation evaluation, adherence could theoretically be more indicative of clinical response to the algorithm, whereas retention could characterize patient buy-in of the implementation. Secondary outcomes will include the percentage of patients starting LAIB for the first time, illicit use of substances per self-report and toxicology, and results of infectious disease while in the program.

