### Evaluation procedures, data sources, and variable abstraction

Evaluation procedures are limited to review of medical records that will already be in existence. The evaluation will include participants who received treatment for OUD between 6/1/2022 and 1/1/2024 and a random sample of patients without OUD within the same date range. Follow up information will be included on all participants up until 1/1/2025.

Data will be collected through retrospective chart review of the ICC’s electronic medical record. Corresponding to the listed date ranges, these data will be measured at six months before implementation of MOUD 2.0 and six months after implementation. Data will then be de-identified and sent to team members for analysis.

Demographics and medical history will have already been included in the electronic medical record from the standard intake forms used to begin patient encounters. Variables to be abstracted from the medical record include:

Demographic information: age, sex, racial self-identification.Adherence to MOUD (categorical, based on positive buprenorphine toxicology or concurrent negative opioid and buprenorphine toxicology) at collection time point.Use of opioids during treatment periods.Months in MOUD program, up to 1 year.Month/year of MOUD visits.Month/year of LAIB injection.Results of urine drug screens while in program.Treatment Effectiveness Assessment Score (21).Results of HIV/HCV screening labs while in program.Dates, dosage, and quantity of buprenorphine prescriptions.

Adherence is difficult to determine from self-report in patients with OUD due to factors like diversion, stigma, and bias (26, 27). Previously published non-LAIB algorithms did not incorporate objective measures besides self-report. To improve accuracy in treatment, adherence will be determined based on toxicology as described in the algorithm.

The approach to urine drug screening was non-standard in the months prior to implementation and continues to reflect the harm reduction approach to treatment. Therefore, adherence will be operationalized as having a minimum of 3 buprenorphine- and norbuprenorphine-positive (“appropriate”) drug screens over a 6-month period regardless of substance use. Each screen should be at least 2 weeks apart within this time period. In each phase of the evaluation, participants will be dichotomized into “adherent” vs “non-adherent” using the above definition.

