### Data analysis

Baseline and demographic characteristics will be summarized with descriptive statistics such as means and standard deviations for continuous variables such as age and percentages for categorical variables such as race.

To accommodate the need for OUD treatment centers to have fair and ethical treatment of patients at the clinic-wide level, we will use patients as their own controls and assess six-month adherence before and after program implementation. The evaluation will follow the same patients, either adherent or non-adherent at six months before algorithm implementation, by chart review to see if they crossed over to the opposite outcome six months after implementation. We will present adherence at endpoints six months prior to and six months after MOUD 2.0 implementation as proportions. We will qualitatively compare the proportion of adherence six months prior, i.e. adherence in 2022, to the proportion six months after. Then, a chi-squared test will compare discordant pairs, i.e. patients who became newly adherent after MOUD 2.0 and patients who became newly non-adherent.

Because we are treating adherence as a binary outcome, we will use McNemar’s test to determine differences in adherence before and after implementation, with each individual patient before and after implementation as a paired sample. The Chi-squared test statistic for McNemar’s test takes the form:

$$\chi^{2}=\frac{{\left(b-c\right)}^{2}}{b+c}$$

where χ^2^ follows the chi-squared distribution with 1 degree of freedom, *b* represents the patients who were adherent before and were not adherent after, and *c* represents the patients who were not adherent before and were adherent after.

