Finally, we will present unadjusted six-month survival curves for retention before and after implementation. While comparing unadjusted survival curves before and after MOUD program implementation has potential for survival bias (i.e., individuals need to “survive” to program implementation in order to be considered for post-implementation calculations), this comparison is given to provide a general sense of how MOUD 2.0 might affect the clinic overall and not to predict explicit dropout rates. If there is a significant number of patients not retained, descriptive statistics for this group will be reported to characterize factors associated with dropout. Secondary outcomes such as receipt of LAIB and use of opioids and of other substances during the evaluation periods will be analyzed with linear regression models for descriptive purposes. These primary and secondary outcomes may also be used for a future stepped wedge analysis in other clinics that could use the algorithm prospectively.

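### Dropout factors are to be described in the non-retained patients alone, behind an undefined trigger, so the planned table cannot by itself show an association or its direction

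*Protocol article*

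**What the plan says.** Study objectives makes retention one of the two primary outcomes and defines it as "at least 180 days of continuous pharmacotherapy with a medication prescribed for OUD, with no gaps greater than seven days". Data analysis gives it one main display: "we will present unadjusted six-month survival curves for retention before and after implementation". The same paragraph then adds the dropout analysis: "If there is a significant number of patients not retained, descriptive statistics for this group will be reported to characterize factors associated with dropout".

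Three other statements bear on whether a comparator exists:

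- The overall summary, in Data analysis: "Baseline and demographic characteristics will be summarized with descriptive statistics". It is not split by retention status.
- The only regression models named: "Secondary outcomes such as receipt of LAIB and use of opioids and of other substances during the evaluation periods will be analyzed with linear regression". Retention is not listed as an outcome for them.
- The variable list in Evaluation procedures, data sources, and variable abstraction. It opens with "Demographic information: age, sex, racial self-identification" and goes on to months in the program, opioid use, urine drug screens, injection month, Treatment Effectiveness Assessment score, HIV/HCV results and buprenorphine prescription details.

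**The concern.** The sentence sets a purpose that its method cannot serve. A factor is associated with dropout if it is more, or less, frequent among those who leave than among those who stay. The plan describes only those who leave. A characteristic that is merely common in this clinic will be common among the non-retained too, and the stated purpose invites a reader to take it for a dropout factor.

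The trigger, "If there is a significant number of patients not retained", has no count, percentage or test behind it. Whether anything is reported about patients who leave is therefore decided after the number is known.

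This is the plan's only stated analysis of who is lost. Retention is a primary outcome, and Table 1 of the article includes referral or discharge among the algorithm's own actions, so who leaves is a natural question for readers. What is at stake is the interpretation of an exploratory table, not the main results.

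**Working it through.** **Is there a comparator elsewhere?** The retention curves are unadjusted and carry no patient characteristics. The linear regressions are for secondary outcomes. The baseline summary is pooled over retention status. The random sample of patients without OUD, mentioned under Evaluation procedures, has no MOUD retention to compare. The article therefore states no retained-versus-non-retained comparison.

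**Inputs.** N = 100 is the approximate number given under Setting and population. The dropout proportion is not given; 30% is assumed, so 30 patients are not retained and 70 are. The factor share among the non-retained is also assumed: 60%, so 18 with the factor and 12 without. No figure in the plan has to be reproduced here; the calculated sample size of 86 has no bearing on this analysis.

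**Formula.** With p the factor share among the 70 retained patients:

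RR = [18 / (18 + 70p)] ÷ [12 / (12 + 70(1 − p))]

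| Share in retained (p) | Dropout risk with factor | Dropout risk without | RR | Overall share |
|---|---|---|---|---|
| 75% | 18/70.5 = 25.5% | 12/29.5 = 40.7% | 0.63 | 70.5% |
| 60% | 18/60 = 30.0% | 12/40 = 30.0% | 1.00 | 60.0% |
| 45% | 18/49.5 = 36.4% | 12/50.5 = 23.8% | 1.53 | 49.5% |
| 25% | 18/35.5 = 50.7% | 12/64.5 = 18.6% | 2.73 | 35.5% |

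The planned output is the same in every row: 60% of the non-retained have the factor. The rows run from lower risk with the factor, through no association, to higher risk.

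**Does this depend on the assumed 30%?** No. With a factor share of 70% among the non-retained, and 20 to 50 of 100 patients not retained, the risk ratio is:

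- 1.99 to 1.56 if 50% of the retained have the factor;
- 1.00 if 70% have it;
- 0.51 to 0.68 if 85% have it.

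The size changes, but the ambiguity of direction does not.

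**What would a side-by-side table give?** Take the 45% row. The difference is 60% − 45% = 15 points. Its standard error is √(0.60·0.40/30 + 0.45·0.55/70) = √(0.00800 + 0.00354) = 0.107, so the 95% interval is 15 ± 21 points, about −6 to +36. The direction of the estimate becomes readable, but precision is poor. Likewise, the power to detect 70% versus 50% at two-sided 0.05 is about 35%, 45%, 51% and 53% with 20, 30, 40 and 50 non-retained patients. These figures are for all 100 patients, before any split by period.

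**The case against.** The strongest reply is that the retained group may be recoverable. If the overall baseline summary covers the same patients and variables, retained equals total minus non-retained. In the table above, the overall shares of 70.5%, 60.0%, 49.5% and 35.5% separate all four cases. This stands, and it rules out the stronger reading that no association could ever be seen. It has limits: the plan does not name that summary as the comparator, it may not include the clinical variables, and the subtraction works only if both tables rest on the same patients.

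Other inferences are tempting, and the documents do not support them:

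- *Only age, sex and race are available.* They are the only listed demographics; the same list names several clinical variables.
- *The dropout description will not be split into before and after.* The article is silent on this. The sentence follows directly on the before-and-after curves and rules nothing out.
- *A false dropout factor will be reported.* The text promises description, with no test or model. Misreading is a risk, not a stated outcome.

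It is also fair to say that an article condensing a longer protocol commonly leaves out table layout and numerical triggers. That explains the missing threshold in part. It does not explain the one-group method paired with an associational purpose, because both are stated in the sentence itself.

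**Conclusion.** The concern holds in limited form. The planned analysis describes one group, runs only if an undefined number is reached, and is given a purpose that needs two groups. By itself it cannot show whether a factor goes with dropout, or in which direction: under the assumed 30 of 100 not retained and a 60% factor share, risk ratios from 0.63 to 2.73 fit the same output. The 30% and 60% are illustrations, not figures from the plan, and the ambiguity of direction persists across 20% to 50% dropout.

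The importance is minor. The analysis is exploratory, and neither McNemar's test of adherence nor the survival curves for retention depend on it.

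**What to change.** Replace the sentence in Data analysis with wording such as:

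> Characteristics known at the start of each six-month window (age, sex, race, months in program, and, where available, the Treatment Effectiveness Assessment score and urine result at or before window start) will be tabulated side by side for retained and non-retained patients, by period, whatever the number not retained, with differences and 95% intervals. This analysis is exploratory.

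Variables that arise during follow-up, such as LAIB receipt or the last urine result, should not be compared by crude risk ratio. Patients who stay longer have more opportunity to receive an injection or give a later sample, so such a ratio would partly reflect time retained.

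If the authors prefer to keep the one-group description, they should drop the words about factors associated with dropout and call it a description of the patients not retained.

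The cost is one sentence and a somewhat larger table: two retention groups in each of two periods, with differences and intervals. The variables are already on the abstraction list, so no new patients or procedures are needed, although scores and urine results may be missing for some patients at window start. With about 100 patients the intervals will be wide, and wider still within each period.

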### MOUD 2.0 algorithm

The MOUD 2.0 algorithm was implemented at the clinic-wide level in January 2023. Staff at the ICC, Pathways to Housing PA, and PHHS developed the algorithm for use at follow-up visits for OUD after the initial diagnosis visit (see **Table 1** and below **Figure 1**). The algorithm has 4-, 8-, and 12-week decision points to guide treatment for patients with varying responses to sublingual and injectable buprenorphine.

**Table 1 T1:** MOUD 2.0 status and algorithm responses.

Status	Symptoms	Opioid Use	Opioid level	BUP adherence	BUP level	Plan	Visit interval
Full response	Improved	None	Negative	Full	Appropriate	Continue current dose	2 weeks in-person alt 2 week TH option OR 4 weeks in-person
Partial response with BUP	Improved	Some	Positive	Partial	Appropriate	Consider: Increase dose Regular BH f/u LAIB	2 weeks in-person alt 2 week TH option
Partial response without BUP	Improved	Some	Positive	Partial	Negative OR Adulterated OR Late	Review dosing method Consider: Increase dose Regular BH f/u LAIB	2 weeks in-person for up to 12 weeks LAIB or refer at week 12
Minimal or nonresponse without BUP	No improvement	Some	Positive	Partial	Negative OR Adulterated OR Late	Review dosing method Consider: Increase dose Regular BH f/u LAIB	2 weeks in-person for up to 8 weeks LAIB or refer at week 8
Reconsider diagnosis of OUD	Any	Any	Negative	Any	Negative OR Adulterated OR Late	Review hx/reconsider diagnosis of OUD	2 weeks in person Discharge or refer at 4 weeks

“Appropriate” indicates buprenorphine and norbuprenorphine detected in urine without contaminants.

*BUP* buprenorphine, *BH f/u* behavioral health follow up, *LAIB* long-acting injectable buprenorphine, *OUD* opioid use disorder, *alt TH* alternating telehealth.

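### Recorded opioid and substance use can shift after implementation with no patient changing use, because recording stops at programme exit and Table 1 ties some exits to the opioid result; the direction is not fixed

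*Protocol article*

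**What the plan says.** Study objectives lists "illicit use of substances per self-report and toxicology" among the secondary outcomes. Data analysis states: "Secondary outcomes such as receipt of LAIB and use of opioids and of other substances during the evaluation periods will be analyzed with linear regression". It labels these models as descriptive.

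The variable list under Evaluation procedures, data sources, and variable abstraction sets when use is recorded: "Use of opioids during treatment periods" and "Results of urine drug screens while in program". The source is the clinic's own chart: "Data will be collected through retrospective chart review of the ICC’s electronic medical record". The same section says "Follow up information will be included on all participants up until 1/1/2025", but through that same chart.

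Table 1 (MOUD 2.0 algorithm) has three opioid-positive rows:
- With an appropriate buprenorphine level, there is no exit point.
- Without an appropriate level and with improved symptoms, the row ends in LAIB or referral at week 12.
- Without an appropriate level and without improvement, it reads "2 weeks in-person for up to 8 weeks LAIB or refer at week 8".

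The last row covers patients who are opioid-negative without an appropriate buprenorphine level. It ends in discharge or referral at 4 weeks. The text after Figure 1 makes clear that referral is to a different programme.

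Data analysis acknowledges survival bias for the retention curves only.

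**The concern.** When observation ends at programme exit, and exit depends partly on the variable being measured, the patients still observed are a selected group. Here the selection is written into the after period. For the before period the article describes no matching exit rule. It describes tolerance of long gaps between screens and a programme response that lacked consistency.

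The before/after contrast in recorded use therefore mixes two things: change in patients' use, and change in who is still being recorded. The survival-bias caveat concerns patients having to remain until implementation, which is a different mechanism, and it is attached to a different outcome. The adherence comparison is at least restricted to a paired cohort enrolled beforehand; no such cohort is stated for substance use.

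At stake is how a secondary result is read. A lower figure after January 2023 could be taken as less use, and a higher one as harm, when either could come from exits. The article also says these outcomes may be reused in a later stepped wedge analysis.

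**Working it through.** The article gives no figure for opioid use, referral or discharge, so there is no stated result to reproduce. The numbers below are assumptions chosen to show the mechanism. Throughout, no patient changes use, and exits occur only in the after window.

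**Inputs from the article:** about 100 participants (Setting and population); six months before and six months after; exits at weeks 4, 8 and 12 (Table 1).

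**Illustration 1: opioid-positive referrals only.** Assume 100 patients, 40 of them positive throughout, and six monthly screens each. Of the positives, k are referred at week 12 after three screens. There are no other exits.

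| Measure | k = 0 | k = 10 | k = 20 |
|---|---|---|---|
| Positive among those remaining at the end, (40−k)/(100−k) | 40.0% | 30/90 = 33.3% | 20/80 = 25.0% |
| Positive share of screens, [6(40−k)+3k]/[6(100−k)+3k] | 240/600 = 40.0% | 210/570 = 36.8% | 180/540 = 33.3% |
| Any positive screen in the window, all 100 kept | 40.0% | 40.0% | 40.0% |

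The last line does not move because the referred patients were screened before they left. The article does not say which measure will be used.

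**Illustration 2: exits of both kinds.** Assume 20 opioid-positive with appropriate buprenorphine, 10 opioid-positive without, 20 opioid-negative without, and 50 opioid-negative with. Use before is (20+10)/100 = 30.0%. Let half of the second group and all of the third leave. Use among those remaining is (20+5)/(20+5+50) = 25/75 = 33.3%, so recorded use rises.

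With a mix of 20, 30, 10 and 40 and the same exit shares, use before is 50/100 = 50.0%. Among those remaining it is (20+15)/(20+15+40) = 35/75 = 46.7%, so it falls. The sign depends on the mix.

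**Check of the remedy.** Keep all 100 in the denominator and give leavers their last toxicology, or bound them.
- Illustration 1, k = 10: last result 40/100 = 40%; all leavers positive 40%; all negative 30/100 = 30%.
- Illustration 1, k = 20: last result 40%; all positive 40%; all negative 20/100 = 20%.
- Illustration 2, first mix (25 leavers): last result 30/100 = 30%; all positive (25+25)/100 = 50%; all negative 25/100 = 25%.

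In each case the last-result version returns the true value, because use was assumed constant, and the bounds contain it.

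**The case against.** A reader might infer that the bias favours the algorithm, or that the spurious gain is about 3 to 15 points (40−36.8 to 40−25). The documents support neither:

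- The last row of Table 1 removes opioid-negative patients, and at the earliest decision point. That pushes recorded use up.
- Opioid-positive patients with appropriate buprenorphine have no exit point, and those who move to LAIB stay. It is not true that opioid-positive patients as such are referred out.
- Data analysis speaks of use during the periods. Patients in the exit rows have two-weekly visits before they leave, so they would normally contribute after-period data. On an any-use measure with everyone kept, the artefact is zero.
- The outcome is secondary and labelled descriptive, with no stated test.
- The remark about tolerating gaps concerns screening intervals, not the response to a positive result. It does not show that nobody left in the before period, and the before-period retention curve itself allows for dropout.

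All of this stands, and it limits direction, size and weight.

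Two further objections stand only in part. Descriptive statistics on patients not retained are promised, but only if their number is significant, and they are not linked to the substance-use comparison. The denominator could be left to an analysis plan. However, the article itself sets an in-programme recording window beside an exit rule linked to the opioid result, and any later plan would have to deal with that combination.

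**Conclusion.** The point holds as a limit on interpretation. With use recorded only in the programme and some after-period exits depending partly on the opioid result, a before/after difference in recorded use can arise with no change in any patient's use.

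Its sign and size cannot be determined from the article. Under the assumed numbers it ranges from a fall of 15 points among those remaining (k = 20), through zero on the any-use measure, to a rise of about 3 points when opioid-negative exits dominate. These results rest on assumed group sizes and referral shares, on the Table 1 clock starting with the after window, on no exits in the before window, and on constant use. Exits before implementation would reduce or alter the contrast.

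The primary adherence test does not use this outcome. The plan should change because the remedy is cheap and decides what the comparison can show.

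**What to change.** - Analyse opioid and other substance use in the fixed cohort in the programme at the start of each window, and keep all of them in the denominator.
- For each window, report the numbers referred, discharged, lost or unscreened, by last toxicology before exit.
- Show the result with leavers at their last toxicology, and under the two bounds (all leavers positive, all negative).
- Show the in-programme-only result as a secondary version. A retained-and-opioid-negative version may be added, but should not be the main analysis. It merges use with retention, which is already a primary outcome, and scores opioid-negative patients discharged under the last row of Table 1 as failures.
- Extend the survival-bias caveat in Data analysis to substance use.

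The screens, visit months and prescription dates already on the abstraction list should supply this, and no clinical rule needs to change. The cost is a little more derivation work. Use after exit remains assumed, not observed, and the bounds will be wide if many patients leave.

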**Figure 1 f1:**
[figure not shown]
Clinical decision algorithm for treating opioid use disorder with sublingual and injectable buprenorphine.

Patients are clinically categorized as “full response,” “partial response with buprenorphine,” “partial response without buprenorphine,” “minimal or nonresponsive without buprenorphine,” and “reconsider diagnosis of OUD.” Note that “full” or “partial response” in the algorithm refers not to adherence or non-adherent outcomes but are clinical categories of physiological response informing further treatment decisions. Physiological response is important *within* the algorithm but is not an outcome measure for successful algorithm implementation.

Depending on the response, the algorithm recommends a plan and follow-up interval. Categories are based on subjective improvement of OUD symptoms in response to buprenorphine, in combination with objective measures of MOUD adherence. Symptoms include cravings, withdrawals, and interference with other activities and functioning with reference to DSM-5 diagnostic criteria for OUD, and are subjectively reported by the patient as improved, the same, or worse compared to the previous visit.

Because a major goal of MOUD 2.0 is increasing buprenorphine adherence, toxicology is included as a clinical data point to guide decision-making (28). Patients subjectively report non-prescribed opioid use, which is confirmed by urine or saliva drug screen including fentanyl and other opioids. Urine testing for appropriate levels of buprenorphine and metabolites confirms buprenorphine adherence. The combination of subjective patient report, urine opioid screen, and urine buprenorphine testing results in the patient’s status that the algorithm assigns (see **Table 1**).

For example, “full response” patients report improved symptoms, demonstrate appropriate qualitative levels of buprenorphine and its metabolite norbuprenorphine, and show no evidence of opioid use on urine screen. Improved symptoms include findings such as fewer cravings, better functioning in everyday activities, and less time spent for obtaining opioids, etc. (19). These patients continue their regimen of buprenorphine and clinic visits every 2-4 weeks, at shared discretion. Buprenorphine dose will remain unchanged as their current dose and delivery route of buprenorphine appear to be working well.

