### Algorithm development, staffing, and funding in a low-barrier setting

The ICC, the setting for the development of the algorithm, provides medical, behavioral health, substance use treatment, and housing services. Since 2016, the clinic’s services have included low-barrier, primary care-based MOUD. The low-barrier approach was first described with methadone maintenance therapy (29) and has been extended to buprenorphine treatment (30). This approach includes same-day treatment entry, harm reduction, flexibility in appointments and prescribing, and combining services in one location.

The ICC participates in the Pathways housing-first model, which offers immediate access to one-bedroom scattered-site apartments with intensive support services for people with experiences of chronic homelessness. All participants have a diagnosis of a serious mental illness or substance use disorder. Many participants were previously living unsheltered in the Kensington neighborhood of Philadelphia, a neighborhood often called the “epicenter of the opioid crisis,” with high levels of OUD, homelessness, food insecurity, and early mortality (31–33). The ICC continued increasing the number of people treated for OUD and modified its services throughout the COVID pandemic. As multiple other low-barrier MOUD clinics have reported, the ICC MOUD program made several intentional adjustments to MOUD care delivery to facilitate access despite disruptions. Such adjustments included: 1. extended visit intervals of up to 2 weeks during the initiation and stabilization phase of treatment with telehealth options, and, 2. a goal of monthly urine drug screening for all patients, but tolerating longer intervals without penalty.

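### Opioid use is compared per period although testing may differ before and after MOUD 2.0, so recorded use can shift with no change in behaviour

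*Protocol article*

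**What the plan says.** Study objectives lists, among the secondary outcomes, "illicit use of substances per self-report and toxicology". The list of variables in Evaluation procedures, data sources, and variable abstraction includes "Use of opioids during treatment periods" and, as a separate item, the results of urine drug screens. Data cover six months on each side of the January 2023 implementation. Data analysis then says that "use of opioids and of other substances during the evaluation periods will be analyzed with linear regression models for descriptive purposes".

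On testing, four places matter:

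- Evaluation procedures: "The approach to urine drug screening was non-standard in the months prior to implementation and continues to reflect the harm reduction approach to treatment".
- Algorithm development, on the pandemic-era adjustments: "a goal of monthly urine drug screening for all patients, but tolerating longer intervals without penalty".
- MOUD 2.0 algorithm: "toxicology is included as a clinical data point to guide decision-making", and reported non-prescribed opioid use is "confirmed by urine or saliva drug screen including fentanyl and other opioids".
- Table 1: every status row carries an opioid result, and visits are two to four weeks apart.

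Evaluation procedures responds to the uneven screening by defining adherence as at least three appropriate screens in six months, whatever the substance use. It gives no matching rule for substance use.

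**The concern.** A variable that summarises use over a whole period depends on behaviour and also on how often the patient was tested. MOUD 2.0 makes toxicology part of how follow-up is run, so the intervention may change the measurement as well as the behaviour. Using patients as their own controls does not remove this, because the testing changes within the same patient.

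Adherence and use will be read side by side. If use is scored in a way that grows with the number of tests, the evaluation could report better adherence with more illicit use, or miss a true fall in use, when part of the change comes from testing. Data analysis warns of survival bias in the retention curves, and the limitations in the Discussion mention confounding in general. Neither mentions unequal testing. Data analysis also says these outcomes may be reused in a stepped wedge analysis, where the same shift in detection could recur.

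**Working it through.** The documents give no figure for this outcome, so there is none to reproduce. The check asks how far recorded use can move when true use does not.

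**Inputs**

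- Period length: six months, about 26 weeks, on each side (Evaluation procedures).
- Screens before: 6 if the monthly goal was met, fewer if the tolerated longer gaps occurred. This is an assumption, because the goal describes the pandemic adjustments and no rate is stated for the second half of 2022.
- Screens after: 26/4 = 6.5, taken as 7, if one screen goes with each four-weekly visit; 26/2 = 13 if one goes with each two-weekly visit. This is also an assumption, because Table 1 gives visit intervals and not screening intervals.
- Chance p that a screen is opioid-positive: 10%, 20% or 30%, the same in both periods (assumption).

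**Any-positive scoring.** P(at least one positive in m screens) = 1 − (1 − p)^m. For p = 20%: 1 − 0.8^6 = 73.8%, 1 − 0.8^7 = 79.0%, 1 − 0.8^13 = 94.5%.

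| p | 6 screens | 7 screens | 13 screens | Rise, 6 to 7 | Rise, 6 to 13 |
|---|---|---|---|---|---|
| 10% | 46.9% | 52.2% | 74.6% | 5.3 points | 27.7 points |
| 20% | 73.8% | 79.0% | 94.5% | 5.2 points | 20.7 points |
| 30% | 88.2% | 91.8% | 99.0% | 3.5 points | 10.8 points |

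(Differences are taken before rounding.) With longer gaps before, 4 versus 7 screens gives 34.4% to 52.2%, 59.0% to 79.0% and 76.0% to 91.8%, a rise of about 16 to 20 points.

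**Patients who differ.** With beta-distributed per-screen risks of mean 20% to 30%, parameters (0.5, 2), (1, 4), (0.5, 1.17) and (1, 2.33):

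- 6 to 7 screens: 52.3 to 55.1%, 60.0 to 63.6%, 63.0 to 65.4%, 72.0 to 75.0%, a rise of about 2 to 4 points.
- 6 to 13 screens: 52.3 to 65.4%, 60.0 to 76.5%, 63.0 to 73.9%, 72.0 to 84.8%, a rise of about 11 to 17 points.

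At the extreme, if 40% of patients screen positive half the time and the rest never do, going from 6 to 12 screens moves the share only from 39.4% to 40.0%.

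**Count scoring.** The mean number of positives is m × p. At p = 20% it is 1.2 with 6 screens, 1.4 with 7 and 2.6 with 13.

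**Adding self-report.** Let s be the chance that self-report alone already records use. Then P = 1 − (1 − s)(1 − p)^m, so the rise is multiplied by (1 − s). For 6 to 13 screens at p = 20%, 20.7 points becomes 14.5 (s = 0.3), 8.3 (s = 0.6) or 2.1 (s = 0.9).

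**Share of screens positive.** If testing is unrelated to use, this stays at p whatever m is, so the spurious change is 0. If it is related, the share moves too. Suppose 30% of patients would screen positive and these were tested twice as often before: 0.3 × 2 / (0.3 × 2 + 0.7) = 46.2% before against 30% after. That is an apparent fall with no change in use.

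**The case against.** The strongest reply is that the artefact needs a scoring rule the article does not give. Nothing in it defines use as any positive result, linear regression would also suit a share of positive screens, and the coding of a secondary outcome is often left to a fuller document. This stands: the rise depends on the scoring. It does not dispose of the point, because the article itself fixes a period-level variable and model for data it describes as non-standard, and adapts a definition to that only for adherence.

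The size is also open to challenge. Thirteen screens requires two-weekly testing throughout. Table 1 allows alternating telehealth for two statuses and four-weekly visits for full response, and it caps the two-weekly schedule at 12, 8 or 4 weeks for the others. The protocol also says the harm reduction approach to screening continues. Thirteen is therefore an upper case, and 6 versus 7 is just as compatible with the text.

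A reader might infer that the comparison is known to be biased against the algorithm, or that a broader panel or a new specimen type adds to the rise. The documents support neither. Actual screen counts are not stated, the earlier panel and specimen are not described, and selective testing before implementation could reverse the direction. For substances other than opioids the algorithm section names no panel, so the link there is weaker.

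**Conclusion.** The concern holds in a limited form. Use is abstracted and analysed per patient-period, the intensity of toxicology can differ between the periods, and the plan does not allow for this in the use outcome. Under any-positive scoring with unchanged behaviour and a common per-screen risk of 10% to 30%, the spurious rise is about 4 to 5 points for 6 versus 7 screens and about 11 to 28 points for 6 versus 13. It is smaller when patients differ in risk or when self-report already captures use. It is zero under share-of-screens scoring with non-selective testing, and the bias can reverse if suspected users were tested more before implementation.

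The screen counts, per-screen risks and self-report values are assumptions, so the true size and direction are unknown. The outcome is secondary and labelled descriptive, and the adherence definition applies regardless of substance use. The primary results are untouched; what is at risk is the interpretation of the use comparison.

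**What to change.** In Data analysis, replace the period-level linear regression for opioid use with a per-screen outcome: the odds that a performed screen is opioid-positive, after versus before implementation, from a logistic GEE or a mixed model with a patient term. Restrict it to analytes tested in both periods. With it:

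- add a sensitivity analysis that keeps at most one screen, the first, per patient per calendar month in both periods;
- report screens per patient-month and the number of untested patients, by period;
- report self-reported use separately from toxicology;
- state that selective testing remains a limitation, since neither the model nor the monthly cap corrects for who was tested and when.

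The cost is analysis wording. Screen results are already abstracted, and screen dates are already needed for the rule that adherence screens lie at least two weeks apart. The downside is that any newly added analytes drop out of the comparison, and some post-implementation screens drop out of the monthly analysis.
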